### Procedure

The study will be disseminated through the presentation of its protocol in meetings with the outpatient services of the HCPA that refer patients to the psychiatry service, such as the internal medicine, pain, and bariatric surgery outpatient clinic.

The researchers will not participate in the indication of treatment of patients or in their assistance. Patients will be sought weekly in the HCPA outpatient medical records and through contact with resident physicians screening new patients. Those who fall into the eligibility criteria will be contacted by phone by the research assistant and invited to participate. It will be explained that refusal to participate will not entail any loss to the treatment. If they agree to participate, they will be asked to attend the HCPA Clinical Research Center (CPC-HCPA), where they will receive the informed consent form, sociodemographic interview, OPD interview, BDNF blood collection, and protocol with self-administered questionnaires. The consent form and OPD will be applied by the researchers. Patients will be contacted by telephone for the follow-up of 6 and 12 months (Figure 1).

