1.1 Clinical domain			
Depression symptoms (BDI)	X	X	X
Anxiety symptoms (BAI)	X	X	X
Psychiatric symptoms (SCL-90-R)	X	X	X

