2.1 Clinical domain			
Diagnosis (review of medical records)	X		
Psychodynamic Diagnosis (OPD-II)	X	X	
			
Comorbidities	X		
Pharmacological treatment	X	X	X
Personality traits (PID-V)	X		X
Number of sessions		X	X
Type of psychotherapy	X		

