##### Domain of Clinical Variables

###### Psychiatry Symptomatology—General Symptomatology

The Symptom Checklist-90-Revised (SCL-90-R) is a self-administered scale consisting of 90 items distributed over nine dimensions: somatization, depression, interpersonal, obsessive–compulsive sensitivity, anxiety, hostility, phobic anxiety, paranoid ideation, and psychoticism. The scales of answers range from 0 (not at all) to 4 (an extreme degree of injury). Over the 6 months after discharge from the clinical follow-up, only paranoid ideation and the psychosis domains are considered. This situation results in a total of 16 items. The next follow-ups are conducted face to face, which allows for the application of the entire checklist (33).

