## Discussion

The only naturalistic longitudinal study that we found concluded that there was no significant difference in outcomes between therapies, as well as among therapists. However, these results need to be viewed with caution given some limitations related to loss, incomplete data, and the lack of long-term follow-up. Our study used direct contact with patients, which increased the number of variables and collection of BDNF as a possible biomarker in response to psychotherapy intervention.

Historically, studies in psychotherapy have been difficult to perform because they involve multiple factors and variables that are interrelated. Many variables may act as only associated factors, and others (e.g., mediators, predictors and even as confounders) may have varying effect sizes. We had difficulty defining some variables as mediators or confounders because the mechanism by which psychotherapies work is a matter of debate (54). We are interested in determining what is common to all psychotherapies. Therefore, we relied on published studies (16) and clinical experience.

Regarding the biological factors, studies of biomarkers such as BDNF may provide insights into the possible mechanisms of illness and recovery from serious disorders such as depression, bipolar disorder, and schizophrenia (22). A few studies have evaluated this neutrotrophin in the context of psychotherapies (29, 55). However, the mechanisms by which long-term psychotherapies produce changes in neuronal circuits and biomarkers, such as BDNF, have not yet been determined. In addition, most existing studies are characterized by follow-up durations of fewer than 12 weeks. As a result, they may be unable to detect changes that occur more slowly than those observed in BDNF with psychotropic drugs (56).

Considering the severity profile of patients referred to a tertiary medical center and the level of experience of resident physicians, the magnitude of improvement is lower than in other more favorable clinical settings. This improvement should be more pronounced in the 12-month follow-up considering the long-term effects of psychotherapies. The level of therapeutic alliance may possibly mediate this improvement. We believe that it will also reflect patients’ psychosocial factors and increase BDNF.

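### The mode of follow-up is stated inconsistently, so the 6-month BDNF sample and a full SCL-90-R at follow-up are not secured by the text

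*Protocol article*

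**What the plan says.** Four parts of the protocol article bear on how patients are assessed after baseline.

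- **Procedure.** At entry, eligible patients "will be contacted by phone by the research assistant and invited to participate". If they agree, "they will be asked to attend the HCPA Clinical Research Center (CPC-HCPA"), where consent, a sociodemographic interview, the OPD interview, the BDNF blood draw and the self-administered questionnaires are done. The only sentence on later assessments is "Patients will be contacted by telephone for the follow-up of 6 and 12 months", with a reference to Figure 1.
- **Table 1.** Serum BDNF is marked at baseline and 6 months only. The psychodynamic interview is marked at the same two times: "Psychodynamic Diagnosis (OPD-II) X X". The SCL-90-R is marked at baseline, 6 and 12 months, with no note of a shortened version.
- **SCL-90-R section (General Symptomatology).** For the 6 months following discharge from clinical follow-up, only the paranoid ideation and psychosis items are used, 16 in all. Then: "The next follow-ups are conducted face to face, which allows for the application of the entire checklist".
- **Discussion.** In contrast to an earlier naturalistic study, "Our study used direct contact with patients", and BDNF collection is named as one of the gains.

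The Design section times both follow-ups from study entry.

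**The concern.** These statements do not describe one follow-up procedure. BDNF is taken by venipuncture, so Table 1 needs the patient on site at 6 months, yet the Procedure section gives the attendance step for baseline and leaves it out for follow-up. The SCL-90-R section gives face-to-face contact as what makes the full checklist possible. The shortened assessment before it is therefore, by implication, not face to face.

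Two primary domains are exposed. The biological hypothesis is set at 6 months, and that is the only time after baseline at which BDNF is measured. In the clinical domain, the Aims name general psychiatric symptoms, and the SCL-90-R is the instrument described under general symptomatology. A follow-up score from a fraction of its items cannot be set against a full baseline score.

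**Working it through.** **1. The sections side by side**

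| Source | 6 months | 12 months |
|---|---|---|
| Table 1 | BDNF, OPD-II, SCL-90-R and the other scales | SCL-90-R and the other scales; no BDNF or OPD-II |
| Procedure | telephone contact; no visit described | telephone contact; no visit described |
| SCL-90-R section | 16 items in the 6 months after discharge, then full and face to face | cannot be placed: clock starts at discharge |
| Discussion | direct contact and BDNF collection, mode not given by visit | direct contact, mode not given by visit |

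**2. Two readings of the Procedure sentence**

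- *The call arranges a visit.* This agrees with Table 1 and with how the same paragraph uses telephone contact at entry. It leaves the 16-item assessment in the SCL-90-R section unexplained.
- *The call is the follow-up.* This could account for a shortened checklist, but no blood can be drawn, so it contradicts the BDNF mark in Table 1.

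Neither reading makes all the sections agree.

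**3. What rests on the 6-month blood sample**

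Inputs from Sample Size Estimation and Statistical Analysis: difference 0.22, SD 0.43, two-sided 5%, power 80%, losses 20–30%, 42 per group. Assumption: the SD is that of the within-patient change.

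- Standardised difference: 0.22 / 0.43 = 0.512.
- Pairs needed, normal approximation: ((1.960 + 0.842) / 0.512)² ≈ 30. By paired t test: 31.96, so 32.
- Divided by (1 − loss) at 20%, 25% and 30%: 30 pairs give 38, 40 and 43; 32 pairs give 40, 43 and 46.

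The stated 42 lies within this range, and 3 × 42 = 126. A comparison of two independent groups would need 60 per group before losses and does not reproduce 42. The sizing is therefore for baseline-to-6-month pairs, and each pair needs the second blood sample.

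There is little slack. At 20% loss, 42 × 0.80 = 33.6, so 33 pairs and power 0.81. At 30% loss, 42 × 0.70 = 29.4, so 29 pairs and power 0.76.

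**4. Comparability of a 16-item SCL-90-R**

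- Items: 16 / 90 = 18% of the checklist.
- Dimensions: 2 of 9. Depression and anxiety are among the seven left out.
- Maximum raw sum, at 0 to 4 per item: 16 × 4 = 64 against 90 × 4 = 360.

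A change from the full baseline to the short form has no meaning as a total. Rescoring baseline on the same 16 items would restore comparability, but only for paranoid ideation and psychosis and not for general symptoms.

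**The case against.** The Procedure sentence does not say that the assessment is made by telephone. Earlier in the same paragraph a telephone call is the step before a visit, and the BDNF schedule, the venipuncture, the 6-month hypothesis and the Discussion all fit a visit. Figure 1, cited in that sentence, could not be seen here and may show the mode. The 16-item rule runs from discharge and not from study entry, and it never names the 6-month study assessment. A journal article may also leave visit logistics to the full protocol.

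Most of this stands, and it limits the point. A reader might infer three stronger things that the document does not support:

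- *That the 6-month BDNF endpoint cannot be obtained.* Nothing forbids a 6-month visit, and Table 1 requires one.
- *That power falls by a calculable amount because some patients are followed by telephone only.* The document gives no such share, so any figure would be invented. Such patients might also already be counted within the 20–30% losses.
- *That a change from self-completion to telephone interview biases the before-after contrast.* No section says that any questionnaire is given by telephone.

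The objection does not remove the conflict itself. The attendance step is explicit for baseline and absent for follow-up. The discharge clock does not rescue the SCL-90-R section: the Design and Table 1 contain no assessment timed from discharge, so the rule cannot be mapped to the schedule at all. These are statements that disagree, not detail left to another document.

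**Conclusion.** The point holds as an inconsistency that affects two primary domains, and not as a proven infeasibility. The 6-month BDNF sample, on which the biological hypothesis and the 42 per group depend, is required by Table 1 but not secured by the follow-up text. The SCL-90-R section, followed as written, would produce a score on 16 of 90 items that is not comparable with baseline, while Table 1 shows no reduced form.

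The sample size reproduces, and no figure in the plan changes. The conclusion rests on the text alone. Figure 1 might settle the Procedure sentence, but the 16-item wording in the SCL-90-R section would still need reconciling with Table 1.

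**What to change.** Reconcile the Procedure and SCL-90-R sections with Table 1.

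- **Procedure.** If so intended, state that the telephone call arranges an on-site visit at 6 and at 12 months, where patients complete the same full self-administered forms as at baseline, with the BDNF sample and the OPD-II interview at 6 months.
- **SCL-90-R section.** Remove or correct the wording on a 16-item assessment that is not face to face, and its timing from discharge, so that the instrument and the clock match Table 1 and the Design section.

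The cost is a change of wording. At 6 months it adds no burden, since the scheduled blood sample already requires attendance. At 12 months, on-site attendance may lose a few patients whom a telephone interview would have kept.

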**Figure 1 f1:**
[figure not shown]
Study design.

#### Location

This study will be conducted in the city of Porto Alegre in the state of Rio Grande do Sul in far-southern Brazil. This region has Portuguese, Italian, German, and African influence. It has a population of 1.4 million, and it is the 10th most populous city in Brazil. Its ethnic distribution is as follows: White (79.2%), Black (10.2%), and Pardo (multiracial) people (10.6%). Its religious distribution is as follows: Catholic (83%), Protestant (9%), and others and atheists (8%). Brazil is a country with a high level of religiosity, and it is common for people to associate improvements in their health as being due to their faith (53). The role of religiosity in psychotherapies has not yet been clarified. According to the World Crime Index, Brazil ranks 9th, with Porto Alegre and São Paulo in the 11th and 14th place, respectively; so many patients experience a high level of urban violence and, consequently, severe life stressors related to this.

## Discussion

The only naturalistic longitudinal study that we found concluded that there was no significant difference in outcomes between therapies, as well as among therapists. However, these results need to be viewed with caution given some limitations related to loss, incomplete data, and the lack of long-term follow-up. Our study used direct contact with patients, which increased the number of variables and collection of BDNF as a possible biomarker in response to psychotherapy intervention.

Historically, studies in psychotherapy have been difficult to perform because they involve multiple factors and variables that are interrelated. Many variables may act as only associated factors, and others (e.g., mediators, predictors and even as confounders) may have varying effect sizes. We had difficulty defining some variables as mediators or confounders because the mechanism by which psychotherapies work is a matter of debate (54). We are interested in determining what is common to all psychotherapies. Therefore, we relied on published studies (16) and clinical experience.

Regarding the biological factors, studies of biomarkers such as BDNF may provide insights into the possible mechanisms of illness and recovery from serious disorders such as depression, bipolar disorder, and schizophrenia (22). A few studies have evaluated this neutrotrophin in the context of psychotherapies (29, 55). However, the mechanisms by which long-term psychotherapies produce changes in neuronal circuits and biomarkers, such as BDNF, have not yet been determined. In addition, most existing studies are characterized by follow-up durations of fewer than 12 weeks. As a result, they may be unable to detect changes that occur more slowly than those observed in BDNF with psychotropic drugs (56).

Considering the severity profile of patients referred to a tertiary medical center and the level of experience of resident physicians, the magnitude of improvement is lower than in other more favorable clinical settings. This improvement should be more pronounced in the 12-month follow-up considering the long-term effects of psychotherapies. The level of therapeutic alliance may possibly mediate this improvement. We believe that it will also reflect patients’ psychosocial factors and increase BDNF.

Limitations of this study include the heterogeneity of the training and experience of the resident psychiatrists and the absence of evaluation from their point of view in the psychotherapeutic process. As a study is naturalistic, there is no way to control the impact of the researchers’ interviews. We will collect a series of demographic data, use of medications, and number of sessions to control possible confounders, but we know that because it is an open study, there is no way to control all differences between groups. Also, psychotherapy studies often have large amounts of losses (16). To control this bias, we will compare the clinical and demographic characteristics of the lost sample with those that continue in relation to the baseline. As for the multiplicity of diagnoses that may be found, to homogenize the sample, we will consider for inclusion the BDI value >15.

Studies such as this one seek to contribute to the foundations of public health policies and investments for the treatment of patients with severe mental illnesses who are at risk of hospitalization and suicide. These types of investigations also seek to promote mental health, rehabilitation, and social reintegration. Understanding the mediating and biological mechanisms of the psychotherapeutic process can help to optimize these interventions and facilitate their indication according to the psychopathological profile and the severity of the patients.

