**Methods:**
*Design:* longitudinal, naturalistic. *Participants:* One hundred twenty-six patients who underwent one of three evidence-based modalities of individual psychotherapy [psychodynamic psychotherapy (PDT), interpersonal psychotherapy (IPT), and cognitive–behavioral psychotherapy (CBT)] were included. *Measure:* Primary outcomes are divided into three domains of variables: clinical (general psychiatric symptoms), biological (serum BDNF levels), and psychosocial (resilience, quality of life, coping strategies, social support, and quality of life-adjusted years of life). Confounding/mediator variables included clinical (personality traits, type of psychotherapy, number of sessions, concomitant use of pharmacological treatment, history of previous psychotherapeutic treatment, medical and psychiatric comorbidities, and psychiatric diagnosis), psychosocial (psychosocial stressors, therapeutic alliance, and defense mechanism style), and other (religiosity) factors. *Procedure:* The follow-up period will be baseline and 6 months and 1 year after entering the study. The study will include 42 controls for biological variables only. Sample size calculation considered a significance level of 5% and a power of 80% to detect a difference of 0.22 with a standard deviation of 0.43, assuming losses of 20–30% of patients. The comparison between the modalities of psychotherapy will be by generalized estimating equations (GEE) model, the analysis of mediators by the Hayes method, and confounders by multivariate logistic regression.

**Discussion:** The findings of this study are intended to demonstrate the outcomes of evidence-based psychotherapies for clinical, psychosocial, and biological parameters and to understand the mediators and confounders of this process in a real-life setting for patients with severe mental illness, thus contributing to the establishment of evidence-based public health policies in the field of psychological interventions.

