#### Sample Size Estimation

Our sample size calculation relied on the study of Schaf (51) using BDNF serum levels before and after psychotherapy as outcomes. We arrived at a number of 42 subjects for each psychotherapy and control group, considering a significance level of 5% and a power of 80% difference to be detected 0.22 with a standard deviation of 0.43 and losses of 20–30%. We estimated a total sample size of 126 patients and 42 blood donor healthy controls for biological variable (as comparative of BDNF samples). The inclusion criteria will include having started psychotherapy within 1 month, an age above 18 years, and a BDI score greater than 15. The exclusion criteria will include psychotic disorders, current use of psychoactive substances, cognitive deficits, and dementias.

The study will include a subsample of healthy controls for control of blood samples that were recruited from the HCPA blood bank. The exclusion criteria for the control group included conditions (current or past) that precluded participation in the study (e.g., psychiatric disorders and/or psychiatric treatments), immune disorders, use of immunosuppressants, anti-inflammatory drugs used for fewer than 3 weeks, smoking, abuse and/or drug addiction, and infectious diseases for fewer than 3 weeks.

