#### Statistical Analysis

Shapiro–Wilk test will be used to determine normality. For parametric distributions, dependent or independent *t* tests will be performed. To determine differences between categorical variables, the chi-squared test will be used. For nonparametric distributions, we will use the Wilcoxon test and Mann–Whitney *U* test to compare nonrelated and related means, respectively. A generalized estimating equations (GEE) model will be used to investigate multivariate repeated measurements. The Hayes method will be used to analyze the mediators (52), and the multivariate regression will be used to analyze the confounders. *Post hoc* analyses will be performed using the Bonferroni test.

The data will be expressed as mean ± standard deviation (SD), and a *p* value less than or equal to 0.05 will be considered to be statistically significant (two-tailed). The statistical analyses will be performed using the SPSS version 20.0 software package (IBM^®^, New York, USA).

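### Comparing lost and retained patients at baseline does not control attrition bias, and the named analyses do not in general correct for selective loss

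*Protocol article*

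**What the plan says.** The abstract fixes the sample size "assuming losses of 20–30% of patients", and Sample Size Estimation repeats the figure when it arrives at 42 subjects per group. The limitations paragraph of the Discussion notes that "psychotherapy studies often have large amounts of losses" and gives the response in the next sentence: "To control this bias, we will compare the clinical and demographic characteristics of the lost sample with those that continue", in relation to baseline.

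For the analysis, Statistical Analysis says "A generalized estimating equations (GEE) model will be used to investigate multivariate repeated measurements", and the abstract says "The comparison between the modalities of psychotherapy will be by generalized estimating equations (GEE) model". Statistical Analysis also lists dependent t tests and rank tests for two-group or before–after comparisons. The working correlation of the GEE is not stated. No weighting, imputation or missing-data assumption is named, and no use of the lost-versus-retained comparison in any model is described.

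**The concern.** The article names a threat, names a remedy, and credits the remedy with something it cannot do. A table of baseline characteristics can show that losses were selective on measured baseline variables, but every estimate stays the same whatever the table shows. The allowance for losses in the sample size protects precision and does nothing about bias.

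The main hypothesis in Aims is improvement within each modality. The healthy controls serve the biological variable only, so there is no untreated patient group against which selective loss in the clinical and psychosocial outcomes could cancel. Modality is chosen by personality disorder, number of diagnoses and similar features (Participants). Retention could therefore differ by modality, and the comparison between modalities would then be affected as well.

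**Working it through.** **1. What the loss allowance does.** Inputs from Sample Size Estimation: difference 0.22, SD 0.43, 5% significance, 80% power, losses 20–30%; two-sided from Statistical Analysis. The paired formula gives n = (0.43 × (1.960 + 0.842) / 0.22)² ≈ 30 completers. At 30% loss, 30 / 0.70 = 42.9, i.e. 43, against the stated 42, so the plan's figure is reproduced within one patient. With 42 enrolled, 42 × 0.80 = 33.6 or 42 × 0.70 = 29.4 remain, and paired-t power is about 82% or 76%. That is the whole effect of the allowance.

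**2. What selective loss could do to the named analyses.** The document gives neither the dropout mechanism nor the visit correlation, so these are assumptions. Baseline score Y0 has mean 0 and SD 1, higher being worse. The follow-up score is Y6 = −0.512 + r·Y0 + error, with r = 0.5 or 0.7. The true change is 0.22/0.43 = 0.512 SD, signed as improvement. The log-odds of loss rise by 0.5 or 1.0 per SD of Y0, calibrated to 20% or 30% loss. Let m be the mean baseline score of retained patients. Then:

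- GEE, independence: −0.512 + r·m (retained follow-up mean minus baseline mean of everyone)
- Completer paired change: −0.512 − (1 − r)·m
- GEE, exchangeable: −0.512 + (r − ρ̂)·m, where ρ̂ is the estimated working correlation, close to r

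| Loss | Log-odds per SD | m | r | Independence | Completers | Exchangeable |
|---|---|---|---|---|---|---|
| 20% | 0.5 | −0.096 | 0.5 | −0.560 | −0.464 | −0.513 |
| 20% | 0.5 | −0.096 | 0.7 | −0.579 | −0.483 | −0.513 |
| 20% | 1.0 | −0.173 | 0.5 | −0.598 | −0.425 | −0.518 |
| 20% | 1.0 | −0.173 | 0.7 | −0.633 | −0.460 | −0.520 |
| 30% | 0.5 | −0.143 | 0.5 | −0.583 | −0.440 | −0.513 |
| 30% | 0.5 | −0.143 | 0.7 | −0.612 | −0.469 | −0.514 |
| 30% | 1.0 | −0.253 | 0.5 | −0.638 | −0.385 | −0.521 |
| 30% | 1.0 | −0.253 | 0.7 | −0.689 | −0.436 | −0.523 |

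Extremes against 0.512:

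- Independence: 0.560/0.512 to 0.689/0.512, overstated by 9% to 35%.
- Completers: 0.483/0.512 to 0.385/0.512, understated by 6% to 25%.
- Exchangeable: at most 0.523/0.512, about 2%.

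Two of these analyses err in opposite directions on the same data.

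**3. Three visits.** A large-sample simulation (200,000 patients; correlation 0.5 or 0.7, exchangeable or autoregressive; log-odds 1 per SD; total loss 20–30%) gave these biases in the 12-month change, in SD units. Negative means improvement is overstated.

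| Loss depends on | Independence | Exchangeable | Likelihood, true correlation |
|---|---|---|---|
| nothing | about 0 | about 0 | about 0 |
| last observed score | −0.07 to −0.19 | −0.01 to +0.01 | about 0 |
| unobserved current score | −0.14 to −0.24 | −0.06 to −0.16 | −0.06 to −0.17 |

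**4. What the baseline comparison would have shown.** In the same runs the lost patients were worse at baseline by 0.69–0.79 SD when loss followed the last observed score, and by 0.35–0.64 SD when it followed the unobserved current score. For exchangeable GEE, the smaller baseline difference went with the larger bias. The comparison therefore does not measure the bias, let alone remove it.

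**The case against.** The strongest reply is that the article does not say which GEE will be fitted. With an exchangeable working correlation, ordinary GEE is nearly unbiased when loss depends on observed scores. This stands. A reader might infer from the 35% figure that the planned analysis will overstate improvement by that much. The documents do not support that, because the figure belongs to the independence version only.

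Further points that stand:

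- The 0.51 SD comes from the BDNF calculation. BDNF is expected to rise, and nothing in the article links its level to loss. Here 0.51 SD only sets a scale for a symptom-type score, so the percentages are not shares of any planned symptom effect.
- Stopping therapy is not the same as loss to follow-up. Procedure says patients are contacted by telephone at 6 and 12 months, and the researchers take no part in treatment. The article does not establish that loss is selective.
- The paired tests are listed as general tools. Nothing makes a completer test the primary analysis.
- Missing-data methods are often left to an analysis plan or full protocol, neither of which is shown. Their absence from a condensed article is not the finding.

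What does not stand is the inference that nothing remains. The article makes a positive claim that the baseline comparison controls the bias. A fuller plan could add methods, but that sentence would still be wrong.

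**Conclusion.** The point holds in a limited form. The stated remedy for attrition bias is a diagnostic and controls nothing, and the analyses named alongside it do not in general make up for this. Whether bias arises, how large it is and which way it runs depend on the loss mechanism and the working correlation, and the document gives neither. The figures above are conditional illustrations: from about 2% or less (exchangeable GEE, loss on baseline severity) to 9–35% overstatement (independence GEE) or 6–25% understatement (completers).

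A reader might also infer that replacing GEE by a mixed model settles the matter. It does not. When loss depended on unobserved scores, the likelihood-type estimate was biased by 0.06–0.17 SD, much the same as exchangeable GEE at 0.06–0.16 SD. A sensitivity analysis under not-at-random loss is therefore an essential part of the remedy.

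**What to change.** - **Discussion, limitations:** call the lost-versus-retained comparison descriptive and delete the statement that it controls the bias.
- **Statistical Analysis:** state the missing-data assumption. Analyse each repeated outcome with a method valid under missing at random that uses all observed visits: a likelihood-based mixed model, inverse-probability-weighted GEE, or multiple imputation.
- **Predictors of loss:** use baseline severity, modality, medication and other predictors already collected (Table 1). Aims and the section on mediators and moderators declare therapeutic alliance a mediator. Use it only as an auxiliary variable in the weights or the imputation model, because as a covariate in the outcome model it could adjust away part of the effect under study.
- **Sensitivity:** add one not-at-random analysis, for example with lost patients assigned no change. At 20–30% loss, this multiplies the mean change of retained patients by 0.80–0.70, which bounds the result simply.

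The cost is a little more programming and somewhat wider intervals. No new data or visits are needed.
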